### 8.2.2 Secondary End Points

Secondary endpoints are:

#### Efficacy

- Time from initiation of trial intervention to cessation of eSE within 60 minutes
- Neurological status (including vigilance) 60 minutes after initiation of intervention

- Difference of blood levels of VPA and LEV before and 60 minutes after initiation of intervention
- Recurrence of seizures or nonconvulsive/ convulsive SE after initially successful intervention
- For patients who failed the primary endpoint, number of patients in whom SE ceased during 60 minutes after initiation of intervention according to the treating physician
- For NCSE patients who failed the primary endpoint, time to first cessation, as verified by EEG
- Number of patients with SE-associated ventilation until hospital discharge
- Functional outcome at discharge, defined by Barthel Index (BI) and modified Rankin Scale (mRS)

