## 5.6 Blinding and Unblinding

The trial is a double-blind trial. The trial medication (VAL **or** LEV) will be manufactured by Department Pharmacy of the University Hospital Erlangen (see chapter 5.1). Blinding will also be conducted by the manufacturer.

The randomisation list will be produced by the responsible trial biometrician at the ZKS Leipzig. The original list will contain the allocation of the treatment arm to a corresponding identification number of a study drug package (details to the randomisation process see 8.1.1).

Randomisation will be blinded to the patients and the study site staff. The drugs are both formulated in transparent liquids of the same appearance. Also the running rates of infusion are identical so the blinding can be sustained over the time of intervention.

The unblinding will be implemented by envelopes (sealed and light-proof) provided in the packages. The responsible investigator has to state the time point and reason for unblinding. Also he/she has to confirm in a written form that the unblinding was executed at a time after the end of 15 minutes after the start of the intervention **or** to justify the deviant procedure.

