## **During 45 minutes after T15 - until T60**

- Check for the recurrence of convulsive seizures or minimal rhythmic motor activity or recurrence of EEG signs of NCSE according to Salzburg criteria
- Unblind the medication in case of recurrence of ictal activity (envelope), the subsequent procedure is to be executed in accreditation of the treating physician (as watch and wait/ repetition of infusion with the same antiepileptic drug/ further treatment with another antiepileptic drug)
- Note the time of unblinding (how many minutes after T0? – must be  $\geq 15$  min )

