#### Randomisation procedure

Randomisation lists are created by statistical software. Blocks of randomly chosen length are created as realisations of random samples and stringed together to a list.

ZKS Leipzig delivers one randomisation list per centre each to the central pharmacy Erlangen. Beginning with the first entry in the randomisation list, the staff of the pharmacy packs medication kits for one patient each. Every kit is labelled by a consecutive ID number and contains a sealed opaque envelope revealing the information about the medication. A pre-defined number of kits are packed into a package and are sent to the trial sites. The medical personal in the trial sites is obliged to take the set with the lowest ID number. Treatment failure is defined as clinical evidence of epileptic activity and / or persistent electroencephalographical ictal activity consistent with NCSE according to the Salzburg criteria 15 minutes after the initiation of intervention or recurrence of ictal activity (in case of NCSE return of EEG patterns to baseline status after initial treatment response) during the further 45 minutes observing period which leads to immediate unblinding of medication. In case of treatment success, drug therapy will be unblinded after 60 minutes to ensure appropriate further treatment (see Figure 1). The investigator is responsible that the envelope is not opened before.

Every trial site is equipped first with a start package of fixed number of medication sets. The size of further packages may be adapted in accordance to the accrual of the trial sites.

The trial sites inform the ZKS about every included patient and transfer the medication ID. Matching the randomisation list with the correspondent list from the central pharmacy Erlangen, the ZKS is able to oversee the randomisation process and the medication logistics.

By study design most of the effects in secondary endpoints cannot be unequivocally attributed to the trial medication. Regarding the parameters, they are not susceptible to biased evaluation either. To minimize bias arising from evaluation of EEG-patterns, EEG evaluation trainings shall be performed. Each trial site will be equipped with working instructions to ensure homogeneity of procedures. These working instructions will cover:

1. The preparation of the intervention
2. The procedures during 60 minutes after the start of intervention
3. The procedure of uploading the EEG data
4. The report of AEs.

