## 8.2 End Points

### 8.2.1 Primary End Point

Primary endpoint is the effectiveness of intravenous valproate (VPA) or levetiracetam (LEV) to terminate eSE and maintain control of epileptic activity **up to 60 minutes** after initiation of the trial intervention defined:

- ⇒ for patients with CSE: cessation of convulsions within 15 min after initiation of infusion, subsequent stable cessation of convulsions during 60 minutes after initiation of infusion.
- ⇒ for patients with NCSE: cessation of EEG signs of NCSE according to Salzburg criteria (Leitinger et al. 2016) within 15 min after initiation of infusion, subsequent stable cessation of ictal EEG activity according to the Salzburg criteria during 60 minutes after initiation of infusion as evaluated by the external EEG reference board.

Evaluation of this endpoint is possible for each patient.

Statistically, the time to cessation as well as the success rate is evaluated.

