### 8.5.2 Planned Methods for Analysis

The primary endpoint will be analysed by means of a generalized mixed linear model with binomial link function incorporating randomisation arm as fixed and centers as random effects. Odds ratios are calculated as effect sizes incl. 95% confidence interval (CI) and tested. In secondary analysis, the cessation rates are tested by  $\chi^2$  test. Cessation rates and their difference with 95% CI following Wilson (Newcombe 1998b, 1998a) are calculated.

Other event rates are estimated with 95% CI (Wilson) and possibly are compared by chi-squared test without continuity correction and by mid-p test if expected numbers are too small, respectively. Time-to-cessation is analysed by time-to-event methods (Kaplan-Meier estimates and logrank test).

Latency between start of SE and 1) application of the last benzodiazepines before the start of study medication and 2) start of study medication is analysed by descriptive statistics for CSE and NCSE separately. An adjustment of the primary analysis for these covariates will be considered.

(Generalized) mixed linear models are built for the other endpoints (e.g. questionnaire scores) as well for longitudinal analyses similar to the primary endpoint.

In secondary analysis, the inclusion of the Status Epilepticus Severity Score (STESS, Rosetti et al. 2008) into multiple models for several endpoints is envisaged.

Explorative subgroup analyses are performed for female / male patients, generalized or focal CSE with impaired consciousness/ focal CSE without impaired consciousness / NCSE with coma / NCSE without coma. Although the trial is not powered for these comparisons, the analyses will give valuable new insights on the subtypes of SE and elderly patients.

Due to the short period the patient is in the study, we expect that missing data will be a minor problem. Multiple imputation is envisaged only if a high proportion of questionnaire data is missing. The definition and calculation of derived variables as well as a detailed description of the analysis method is stipulated in the statistical analysis plan. It will be established when data from 10% of the patients are input into the database. This proportion is absolutely necessary to take main properties and relationships of the data into consideration.

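### Time to cessation is followed to 60 minutes although failures may be re-treated from 15 minutes, so as written cessation after a second treatment counts for the allocated arm

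*Protocol*

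**What the plan says.** Protocol 8.2.2 (Efficacy) lists "Time from initiation of trial intervention to cessation of eSE within 60 minutes"; the synopsis calls it a key secondary endpoint. Section 8.2.1 also mentions it: "Statistically, the time to cessation as well as the success rate is evaluated". Section 8.5.2 gives the method: "Time-to-cessation is analysed by time-to-event methods (Kaplan-Meier estimates and logrank test". Section 8.5.1 analyses patients in the arm to which they were allocated, whatever they actually received.

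The primary endpoint uses a shorter window for first cessation. For convulsive status it is "cessation of convulsions within 15 min after initiation of infusion, subsequent stable cessation of convulsions during 60 minutes after initiation of infusion", with an EEG equivalent for nonconvulsive status.

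Section 8.1.1 (Randomisation procedure) sets out what happens to failures. "Treatment failure is defined as clinical evidence of epileptic activity and / or persistent electroencephalographical ictal activity" at 15 minutes, or as recurrence "during the further 45 minutes observing period which leads to immediate unblinding of medication". Under 5.6 the investigator confirms that "the unblinding was executed at a time after the end of 15 minutes after the start of the intervention", or justifies a deviation. Section 6.3 then leaves the next step, before 60 minutes, to the treating physician: watch and wait, or "repetition of infusion with the same antiepileptic drug/ further treatment with another antiepileptic drug".

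No section says how the time-to-cessation analysis treats a patient who received a second treatment before cessation.

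**The concern.** Up to 15 minutes the curve describes the blinded allocated drug. From 15 to 60 minutes it can also contain the effect of a further dose or a different drug, chosen once the allocation is known. An as-allocated logrank test over the whole window credits those cessations to the first drug. The arm with more failures receives more second-line treatment, so if the second treatment works about equally well in both arms, the curves are drawn together. At stake is the reading of a key secondary endpoint: a real difference between the drugs in stopping status could look smaller than it is.

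**Working it through.** **Planning figures reproduced.** Section 8.4 assumes 60% (VPA) and 47% (LEV), two-sided 5% and 80% power. The unpooled formula gives (1.960 + 0.842)² × (0.60×0.40 + 0.47×0.53) / 0.13² = 227.15 per arm, about 454 in total, as stated. The odds ratio is (0.60/0.40)/(0.47/0.53) = 1.69, stated as 1.7. The sample size is sound and is not in question.

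**How many patients could be affected.** Primary failures are 1 − 0.60 = 40% and 1 − 0.47 = 53%: 227 × 0.40 ≈ 91 and 227 × 0.53 ≈ 120, about 211 of 454. These are upper limits. The planning rates are applied to an endpoint that also requires control up to 60 minutes, so failures include patients who ceased on the allocated drug and then relapsed. Those patients already have an uncontaminated event. Patients who are only observed are not contaminated either. The protocol gives no split. If one third of failures were relapses (assumption), at most 40% × 2/3 ≈ 27% and 53% × 2/3 ≈ 35% would be affected.

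**Effect at 60 minutes, no relapses, all failures re-treated, the same rescue success f in both arms (assumption).** Cessation is p + (1 − p)f in each arm, so the difference is 0.13 × (1 − f):

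| f | VPA | LEV | Difference |
|---|---|---|---|
| 20% | 68.0% | 57.6% | 10.4 points |
| 40% | 76.0% | 68.2% | 7.8 points |
| 60% | 84.0% | 78.8% | 5.2 points |
| 80% | 92.0% | 89.4% | 2.6 points |

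**Extreme case.** If every failure is switched to the other trial drug and it works at its planning rate, VPA reaches 0.60 + 0.40×0.47 = 78.8% and LEV 0.47 + 0.53×0.60 = 78.8%.

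**Effect of relapses on the uncontaminated difference.** With one third of failures relapsing, first cessation by 15 minutes is 0.60 + 0.40/3 = 73.3% against 0.47 + 0.53/3 = 64.7%, a difference of 8.7 points instead of 13. The logrank test then has less power even with the corrected event.

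**Logrank power by simulation (227 per arm, two-sided 5%).** First-drug cessation falls within 15 minutes and rescue cessation between 15 and 60 minutes. Power is compared with post-rescue cessation not counted and counted:

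| Scenario (all assumed) | Not counted | Counted |
|---|---|---|
| No relapses, 50% rescue success, half of failures re-treated | about 78% | about 70% |
| No relapses, 50% rescue success, all failures re-treated | about 78% | about 63% |
| One third of failures are relapses | about 47% | about 42% |
| No relapses, all failures switched to the other trial drug at its planning rate | about 78% | about 25% |

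Other plausible timing assumptions move these by a few points; the last scenario ranged from 21% to 26%.

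**The case against.** The protocol does not expressly say that cessation after rescue is an event. Section 8.5.2 leaves derived variables and analytic detail to a statistical analysis plan, and a 60-minute window is compatible with a rule making such cessations non-events. Counting cessation regardless of later treatment is also a recognised treatment-policy approach, and it suits a comparative-effectiveness trial in which total duration of status matters. Section 8.1.1 already concedes that most secondary effects cannot be clearly attributed to the trial drug. Section 8.4 calls the secondary analysis mainly explorative, and 8.2.2 separately reports cessation by 60 minutes among primary failures.

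Much of this stands. It limits the weight of the point, and it makes power an illustration of dilution, not a design failure. It does not remove the point: the protocol fixes the window, the test and the as-allocated attribution, states no treatment-policy aim, and offers no remedy for this endpoint. The obvious later repair, censoring at rescue, would be informative because rescue follows non-response.

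A reader might infer that 40% and 53% of patients will be contaminated and that the planned 13-point difference will vanish. The documents do not support that. The percentages are ceilings, and equality at 78.8% requires complete switching to the other trial drug at full planning efficacy, with no relapses, repeat doses or observation. Section 6.3 speaks only of another antiepileptic drug. Use of the other trial drug is not excluded (5.5.3 does not list it among drugs to avoid, and 6.5 foresees further treatment with a trial drug), but it is not stated either.

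**Conclusion.** The point holds and should be corrected. Followed as written, the endpoint mixes the allocated drug with second-line treatment after 15 minutes. With similar rescue success in both arms the bias is towards no difference; markedly unequal rescue could act otherwise. The loss runs from small (about 47% to 42% power) through moderate (about 78% to 63-70%) to large (about 25%) only in the extreme case. Relapse share, rescue use, rescue success and timing are all assumed, because the protocol gives none of them.

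It would be wrong to extend this to the primary result. A patient who stops only after 15 minutes is already a primary failure, so the success rate, the hypothesis in 8.3.1 and the sample size are untouched. The sentence on time to cessation in 8.2.1 gives the endpoint no confirmatory role.

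**What to change.** In 8.2.2 and 8.5.2, define the event as first cessation before any repeat infusion or other antiseizure or sedative drug. Keep patients who receive such treatment first as non-events to 60 minutes, and do not censor them at rescue. Report cessation regardless of rescue as a descriptive or supportive analysis. Clinical management does not change.

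There are two costs. The main curve no longer describes total duration of status, which the supportive analysis can show. The CRF must also hold the clock time of any second dose within 60 minutes. Unblinding time is already noted (6.3), but the emergency-medication item in 7.1.3 covers only drugs other than the allocated one, so it misses a repeat of the allocated drug. The further-treatment record at Visit 2 does not ask for clock times.

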#### Safety

- Mortality
- Need for any emergency medication (different from allocated study drug) during 60 minutes after initiation of study intervention
- Need for ventilation (noninvasive/ invasive) during 60 minutes after initiation of intervention
- ~~Number of patients with SE-associated ventilation until hospital discharge~~
- Intrahospital complications
  - Incidence of delirium as diagnosed by the treating physician
  - Infections requiring intravenous administration of anti-infectives
  - Adverse events related to infusion/subsequent therapy with antiepileptic drug (sedation, dizziness, nausea, vomiting, thrombocytopenia, leukopenia, hypotension, new elevation of liver enzymes, hyperammonaemia, acute new liver failure or pancreatic damage, tremor, psychiatric abnormalities)

The mRS is the recommended outcome measure in stroke trials as it is directly relevant to the patient's ability to return to daily life. Its scores range from 0 (no impairment) to 6 (death) and include special items as walking and independence that are indicative of the degree to which a patient is competent to participate in daily activities (Lees et al. 2012). As most of the seizures occurring in elder people are caused by an underlying structural brain injury the clinical phenomenology of focal convulsive SE or nonconvulsive SE may imitate stroke-related deficits. Thus, the effects on functional outcome may be quantified meaningfully and appropriately by the mRS. The Barthel Index is also a well-established clinicometric scale which is utilized to reflect elderly patient's need for care in particular and includes basic activities such as transfer and personal hygiene (Mahoney and Barthel 1965).

The secondary endpoints will provide valuable insights into the disorder in this age group. There is a special emphasis on characteristics of SE and concomitant intrahospital complications to provide an equal evaluation of the efficacy and safety of antiepileptic treatment in the elderly.

The combination and comparison of the retrospective and prospective assessment of mRS and BI are chosen in order to quantify its consequences on functional outcome.

#### Determination of primary and secondary measures

All clinical scales (GCS, mRS, BI) are validated and widely used in clinical settings and / or clinical trials. They will be performed by trained neurologists. The pre-mRS and pre-BI reflect the functional status of the patient before the admission to the hospital and will be scored by the patient or a close relative if the patient's capability is impaired. Recurrence of SE or seizures during the hospital stay is defined as witnessed convulsions with or without

impairment of consciousness in case of CSE and the detection of ictal EEG activity in case of NCSE. SE-associated mortality includes all cases of death during the hospital stay even if they are not directly related to SE. The necessity to invasive ventilation is defined as the proportion of patients who have to be ventilated during the hospital stay.

## 8.3 Statistical Description of the trial hypothesis

### 8.3.1 Statistical Hypotheses/Statistical Estimation Method

The trial hypotheses are:

- ⇒  $H_0$ : The frequency of cessation of SE is equal in both arms.  
This is equivalent to the hypothesis: Odds ratio (OR) = 1.
- ⇒  $H_A$  Frequencies of cessation of SE differs between the arms.  
This is equivalent to: OR  $\neq$  1.

Significance level is determined 5% for two-tailed tests.

## 8.4 Sample Size Discussion

Randomised clinical trials on treatment of established Status Epilepticus are rare. The meta-analysis of Yasiry and Shorvon (2014) compares cessation of benzodiazepine resistant SE after treatment with one of five substances which included VPA and LEV. In a second meta-analysis, (Trinka et al. 2015) examined the efficacy of VPA in therapy of established SE. Third, (Alvarez et al. 2011) published results of the registry of benzodiazepine-resistant SE patients. They compared second-line treatments utilizing PHE, VPA or LEV. The reported frequencies of cessation of SE (within variable time frames) vary widely due to different study designs (RCT, prospective open label or retrospective trial, dose schemes, endpoint definition). The cessation rates in our trial with elderly patients are expected to be lower than those reported by (Yasiry and Shorvon 2014): VPA 76% and LEV 68.5%, see e.g., (Zelano and Kumlien 2012). A recent article (Misra et al. 2017) reports 70% response for VPA treatment.

New articles (Beuchat et al. 2018, Kapur et al. 2019, Sánchez Fernández et al. 2019) do not eliminate the indecision between the standard drugs for stage II. The systematic review and meta-analysis from Sánchez Fernández reports 70% success for VPA and 62% for LEV.

Omitting the studies of pediatric SE and with first-line treatment of SE, an odds ratio OR = 1.7 in favour of VPA vs. LEV is calculated, which seems much more realistic than the reported OR = 2.7 for SE cessation in (Alvarez et al. 2011). The OR = 1.7 applies for cessation frequencies of 60% (VPA) and 47% (LEV). Assuming these rates, a significance level of 5% and a power of 80%, the R (R Core Team 2017) package TrialSize calculates for chi test a sample size N = 454.

All patients are monitored in an appropriately equipped environment (emergency room, intermediate care, intensive care unit or similar). Therefore, maximal 5% drop-outs are expected (cf. 6.4.2). Assuming a drop-out rate of about 5 %, a total of **477 patients** are to be randomized.

The secondary endpoints will provide valuable insights into the safety of both treatments. Additionally they will provide an important source for characteristics of the disorder in elderly patients. However, this analysis is mainly explorative and power estimation is not sensible.

## 8.5 Statistical Methods

### 8.5.1 Analysis Population

Primary analysis bases on the full-analysis set (FAS), that is, all patients who received trial medication. The patients are analysed in the arm they were allocated independently from the actual treatment. This follows the intention-to-treat principle.

The per-protocol set (PPS) consists of all patients who pass through the study according to the TP. Patients for whom the diagnosis NCSE was not confirmed by the central EEG review will be excluded from the PPS. Per-protocol analysis is done as a sensitivity analysis. However, if PPS is 95% or more from the FAS, a PP analysis is dispensable.

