## **11 REFERENCE EVALUATIONS**

All study related electroencephographical data will be evaluated by a central committee consisting of two external expert reviewers (EEG reference board) who are medical specialists in neurology and also experts for epileptology. They are blinded to the treatment; clinical data of the patient will not be provided. For the purpose of the external review every trial site transfers the pseudonymized EEG data to a study specific cloud, the related server is located at the ZKS Leipzig. Access to the EEG data is restricted to the reviewers. Each trial site is only permitted to upload data. The pseudonymisation can be realized in the following manner:

- ⇒ the clinical recording of a patient will be stopped and a new record labelled with the patient ID, will be started
- ⇒ after converting the data in an edf file the heading with the patient related information can be read out in a text editor and pseudonymisation can be checked before the transfer to the cloud

Reference evaluation of the EEGs will be completed within 1 month. Disagreement between the two expert raters will be resolved by discussion. If the EEG reference board disagrees with the diagnosis NCSE in more than 25% of all cases contributed by a given trial site over a year the trial staff of that site will undergo additional training.

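### NCSE cases that the EEG board does not confirm stay in the primary analysis, probably often as successes, and the one planned analysis without them may be skipped

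*Protocol*

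**What the plan says.** **Analysis sets.** Section 8.5.1 makes the FAS primary: every patient given study drug, analysed as allocated. On misdiagnosis it says "Patients for whom the diagnosis NCSE was not confirmed by the central EEG review will be excluded from the PPS". The per-protocol analysis is a sensitivity analysis, and "if PPS is 95% or more from the FAS, a PP analysis is dispensable".

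**Endpoint.** For NCSE patients, section 8.2.1 asks for "cessation of EEG signs of NCSE according to Salzburg criteria" within 15 minutes and stable to 60 minutes, as judged by the external EEG reference board. The T15 entry in section 6.3 defines cessation by what is absent from the EEG. Neither place requires the board to have found an ictal EEG beforehand. Section 8.2.1 adds that every patient can be evaluated.

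**Board.** Section 8.1.1 has the diagnostic EEGs re-read by two blinded external raters. Section 11 calls such a pair the EEG reference board and orders more training "If the EEG reference board disagrees with the diagnosis NCSE in more than 25% of all cases contributed by a given trial site", counted annually.

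**Sample size.** Section 8.4 assumes 60% (VPA) and 47% (LEV) and "a significance level of 5% and a power of 80"%, giving N = 454 evaluable. With about 5% drop-out, 477 are randomised. No allowance is stated for patients who turn out not to have NCSE.

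**Ineligible patients.** Section 6.2.3 leaves FAS membership of a patient later found ineligible to a discussion between the investigator and the biometrician.

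**The concern.** An endpoint defined as the absence of a pattern is easily met by a patient who never had the pattern. If the board sees no NCSE on the entry EEG, it will often see none during the hour after infusion, whichever drug was given. Such patients carry little information about the drugs but count in both arms of the primary comparison.

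Two results are at stake. One is the comparison: a treatment-independent subgroup shrinks the difference. The other is each drug's own success rate. Sections 1.2.1 and 8.7 justify completing the full sample by the need for reliable estimates even if no difference is shown, and a larger sample does not remove inflation of the rates.

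The protocol has reason to expect such cases. Section 1.1 calls NCSE frequent in older people, hard to diagnose, and overlapping with delirium and dementia. Yet the only planned analysis that leaves these patients out is optional under the 95% rule.

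**Working it through.** **Inputs from the protocol.** Rates 60% and 47% and N = 454, so 227 per arm (section 8.4); 1:1 allocation (section 8.1.1); "Significance level is determined 5% for two-tailed tests" (section 8.3.1).

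**Reproducing the stated N.** Unpooled formula, per arm:

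n = (1.960 + 0.842)² × (0.60×0.40 + 0.47×0.53) / 0.13² = 7.849 × 0.4891 / 0.0169 = 227.15

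This is 454 in total when rounded to the nearest patient. The pooled formula gives 230 per arm, 460 in total. Pooled power at 227 per arm is 79.5%. The odds ratio is (0.60/0.40)/(0.47/0.53) = 1.69, matching the stated 1.7. The plan's figure stands.

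**Dilution model.** Let f be the unconfirmed share of the FAS, that is, NCSE share × non-confirmation rate. Neither factor is in the protocol, so f is assumed. For example, 20% × 5% = 1%, 50% × 10% = 5% and 40% × 25% = 10%. If these patients succeed in both arms and the rest follow the planned rates, each rate becomes p′ = (1 − f)p + f, and the difference becomes (1 − f) × 13 points. At f = 5%: 0.95×0.60 + 0.05 = 62.0% and 0.95×0.47 + 0.05 = 49.65%, a difference of 12.35 points.

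| f | VPA vs LEV | OR | Power, 227 per arm | Power if these patients are left out | Total N for 80% (pooled) |
|---|---|---|---|---|---|
| 0 | 60.0% vs 47.0% | 1.69 | 79.5% | 79.5% | 460 |
| 1% | 60.4% vs 47.5% | 1.68 | 78.8% | – | 470 |
| 2.5% | 61.0% vs 48.3% | 1.67 | 77.6% | 78.5% | 482 |
| 5% | 62.0% vs 49.7% | 1.65 | 75.6% | 77.4% | 506 |
| 10% | 64.0% vs 52.3% | 1.62 | 71.6% | 75.2% | 556 |

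**Sensitivity to the assumptions.**
- If all 477 are analysed (238.5 per arm), power is 81.4% at f = 0, 77.7% at 5% and 73.7% at 10%.
- At f = 5%, power is 75.6% if all unconfirmed patients succeed, 75.3% if 53.5% do, and 75.1% if none do. The power loss comes from the lack of a drug effect in these patients. Their success is what raises the two rates.

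**The waiver.** It can apply only when all exclusions from the PPS together are at most 5% of the FAS, so f is then at most 5%. The largest power loss it could leave unexamined is 79.5 − 75.6 = 3.9 points, and that needs no other protocol deviation in the trial. At larger f the per-protocol analysis has to be done. However, it also removes every other deviation, so it does not isolate the effect of misdiagnosis.

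**The case against.** A reader might infer that unconfirmed patients succeed automatically and that the trial therefore does not have its stated 80% power. The documents support neither.

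- **Diagnosis and cessation are not mirror images.** Under section 4.1, discharges at or below 2.5 Hz need an extra feature (fluctuation, evolution or a subtle clinical sign) to count as NCSE. Under section 6.3, any rhythmic epileptiform discharges lasting 10 seconds rule out cessation. A patient rejected for lacking the extra feature can still be scored a failure. Section 8.1.1 also counts clinical epileptic activity as failure, and section 6.3 starts a new EEG recording before the infusion. Success is likely for many, not certain.
- **Unconfirmed does not always mean absent.** The board receives no clinical data (section 11), and section 4.1 allows a clinical diagnosis when no EEG is available. Some of these patients may have NCSE and respond to treatment, so a zero drug effect in all of them is the extreme case.
- **The rates are unknown.** The 25% in section 11 triggers site retraining. It is neither an expected rate nor a cap. Section 8.4 also does not say that 60% and 47% refer to confirmed cases only.
- **The FAS is a sound primary set.** It follows the stated intention-to-treat principle and suits a comparative effectiveness trial. Making a post-randomisation exclusion primary, decided by a board without clinical data, would be a debatable trade for a small gain (77.4% against 75.6% at f = 5%).

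All four points stand. They limit the size of the problem and rule out changing the primary set. They do not justify an option to omit the only planned analysis that shows how much unconfirmed cases matter.

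**Conclusion.** The point holds in a limited form. Unconfirmed NCSE cases remain in the primary analysis, the endpoint makes success likely for many of them whichever drug they received, the sample size does not consider them, and the analysis without them is optional up to a 5% exclusion share.

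The size depends on f, which the protocol does not give. The power loss is under 1 point at f = 1%, about 4 points at 5% and about 8 points at 10%, if all unconfirmed patients succeed in both arms and the planned rates hold in everyone else. On the same assumptions, at f = 5% VPA would read 2.0 points and LEV about 2.7 points too high. Up to about f = 2%, power stays within roughly 2 points of 80%. The sample size calculation contains no error, and a real shortfall in power is possible but not shown. This is a cheap improvement to reporting, not a flaw in the choice of primary analysis.

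**What to change.** 1. Keep the FAS as the primary set.
2. In section 8.5.1, delete the rule that lets the per-protocol analysis be omitted when the PPS is 95% or more of the FAS.
3. Always report, beside the FAS result, the same model on the FAS without EEG-diagnosed NCSE cases that the board rejects on the pre-infusion EEG alone, read blind to arm and later course. Cases without a diagnostic EEG stay in.
4. Reconcile section 6.2.3 with section 8.5.1, so that FAS membership follows one fixed rule. Under section 8.1.1 the drug is unblinded at 60 minutes at the latest, so the investigator may know the arm when a case-by-case decision is made.
5. Optionally, show in section 8.4 how power varies over an assumed unconfirmed share.

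The cost is protocol wording and one extra sensitivity analysis, since section 8.1.1 already has the diagnostic EEGs re-read. The extra result may differ slightly from the primary one, so the text should say beforehand that the FAS result decides.
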